**Appendix I : List of definitions 29**

**1 Introduction**

- 1. **Background**

Urinary tract infections (UTIs) occur frequently. The incidence of UTIs in a Dutch family doctor’s practice is about 30 to 40 per 1000 patients per year. Eighty to ninety percent of UTIs affect women (1). One in three women will have at least one UTI by the age of 24 years, and 40-50% of women will experience at least one UTI during their lifetime. The frequency of UTIs increases with age while, for example, patients with a urinary catheter, diabetes mellitus, spinal cord lesions, or a neurogenic bladder are particularly susceptible (2). Due to the increasing life expectancy and the increasing number of patients suffering from diabetes, it is to be expected that the prevalence of UTIs will rise (3).

In addition to the impact on quality of life, UTIs have financial implications (3;4). Although the costs associated with a single episode of UTI are relatively low, due to the high incidence total costs are estimated to be around 100 to 300 million Euro per year in the Netherlands (5).

It is of note that 20 to 30 percent of the women experiencing an episode of UTI will experience recurrent UTIs. Recurrent UTIs (RUTIs) are usually defined as at least three episodes of UTI in the previous twelve months or two episodes in the previous six months(6). RUTIs can be based on a “relapse” after treatment cessation with the pre-therapy isolate or as a “reinfection” with a different organism after initial treatment cessation (2). Long-term low-dose antibiotic prophylaxis can be recommended for prevention of reinfections in women with UTIs (7).

- 1. **Rationale**

Randomized trials (RCTs) have documented that continuous prophylaxis with trimethoprim-sulfamethoxazole (TMP-SMX) diminishes recurrences by 95 percent (from 2 to 3 episodes per patient-year to 1 or 2 episodes per 10 patient-years) (8). However, these successes may not last another decade now that antibiotic resistance is increasingly becoming a problem. The most important risk factor for having a UTI resistant to TMP-SMX is its recent or present use (9). During a 2-week follow-up study in healthy students, who took TMP or TMP-SMX prophylaxis, a total number of 82 out of 86 students developed resistant micro-organisms in their faeces (10).

It is known from clinical practice that many women are afraid of getting resistant bacteria. For that reason they do not want to take antibiotic prophylaxis over an extended period of time. Furthermore, antibiotics can cause adverse side effects. Therefore, the need for alternatives to antibiotic UTI-prophylaxis is evident. Knowledge of the pathogenesis of UTIs is essential to prevent infection from a small number of microbes which originate from outside the urinary tract (primary prophylaxis). Two essential steps in the pathogenesis of UTI are: colonization and adherence of uropathogens.

### UTIs result almost exclusively from the ascending route. Bacteria colonizing the perineum and vagina can enter the urethra and further ascend to the bladder or even the kidneys. The colonization can be inhibited by the normal vaginal flora: lactobacilli*,* which produce lactic acid, and maintain a low vaginal pH that inhibits the growth of many uropathogens. In postmenopausal women lactobacilli disappear. This results in a higher chance of colonization of the vagina with *Enterobacteriaceae*. It has been demonstrated that vaginal colonization with *Escherichia coli* and the absence or low levels of vaginal lactobacilli were independently associated with a history of a recent UTI (11). It has also been shown that oral administration of *Lactobacillus rhamnosus GR-1* and *L. reuteri RC-14* restores normal vaginal lactobacilli flora and reduces colonization by potential pathogenic bacteria (12). In a RCT with postmenopausal women with a history of recurrent UTIs, the incidence of UTIs was reduced in the estriol treated group compared to the placebo group (0.5 *versus* 5.9 episodes per patient year; p<0.001). More specifically, the topical application of vaginal estriol cream in the treatment group led to re-colonization of the vagina by lactobacilli in 23 of the 36 women. There was a strong positive relation between vaginal colonization status and the risk of infection: No UTIs developed in 20 of the 23 women who were colonized with lactobacilli (success rate of 87 percent) compared with 6 out of the 13 (success rate 46%; difference 41 (95%CI from 10 to 71) who were not colonized with lactobacilli (13).

### The adherence of uropathogens to the bladder mucosa is another essential step in the pathogenesis of UTIs. In that process, adhesins (fimbriae) are important virulence factors. Although virulence factors have been characterized best in *Escherichia coli* (the most prevalent uropathogen) many of the same principles are applicable to other Gram-negative uropathogens. Cranberries contain fructose and proanthocyanidine, which inhibit the adherence of type 1 fimbriae of *E. coli* (the most important virulence factor in cystitis) and the expression of P fimbriae (the most important virulence factor in pyelonephritis), respectively (14;15). In a RCT with pre-menopausal women, the incidence of UTIs in the cranberry-treated women was only 16% (versus 36% in the control group; difference 20%; 95%CI from 3% to 36%; p=0.023), during a 6 months follow-up (16). Furthermore, it has been demonstrated that cranberry juice may also offer protection against resistant strains of *E. coli* by a mechanism that is not likely to increase selective pressure associated with antibiotic resistance (17).

- 1. **Purpose**

To quantify the effect of antibiotic prophylaxis compared to two non-antibiotic prophylaxis modalities on the incidence of symptomatic UTIs in pre- and post-menopausal women with recurrent UTIs. In addition, we assess differences in the development of bacterial drug resistance.

**2 Study objectives and endpoints**

**2.1 Study objectives**

**2.1.1 Primary objectives**

- To determine if non-antibiotic prophylaxis is a non-inferior treatment in the prevention of recurrent symptomatic UTIs compared to the currently standard antibiotic prophylaxis in pre- and post-menopausal women (non-inferiority trial)
- To assess if non-antibiotic prophylaxis reduces the selection of antibiotic resistant micro-organisms in urine and faeces compared to currently standard antibiotic prophylaxis in pre- and postmenopausal women
  - 1. **Secondary objectives**
- To evaluate if non-antibiotic prophylaxis compared to antibiotic prophylaxis in pre- and post-menopausal women lead to differences in the:

- incidence of asymptomatic bacteriuria

- incidence of other (non-urinary tract) infections

- incidence of adverse events

- quality of life

- To evaluate the costs and cost-effectiveness of non-antibiotic prophylaxis compared to antibiotic prophylaxis in the prevention of recurrent UTIs in pre- and post-menopausal women.

**2.2 Study endpoints**

**2.2.1 Primary endpoints**

- the numbers of recurrences of symptomatic UTI

- time to first occurrence of antibiotic resistance in urine or

faeces

**2.2.2 Secondary endpoints**

- incidence of asymptomatic bacteriuria

- incidence of other infections

- adverse events

- quality of life

- costs per prevented UTI

**3 Methodology**

- 1. **Study design**

The NAPRUTI study consists of two trials: RCT-A and RCT-B. Premenopausal women will be included in RCT-A, postmenopausal women in RCT-B. Both trials are multi-center, randomized double blind clinical trials with a follow-up time of 15 months.

Both trials consist of two parts: part one deals with UTI recurrence (non-inferiority part); part two aims to show a difference with respect to the development of bacterial drug resistance.

- 1. **Study duration**

Both trials will recruit 280 women. Patient enrolment is anticipated to last 2 years. After randomization patients will be followed for 12 months during which they will receive study medication and 3 months afterwards (“wash-out”-period). Total study duration will be 48 months.

**3.3 Randomization and blinding**

**3.3.1 Method of randomization**

In both trials, computer-aided and concealed block randomization with pre-stratification by center and presence of a uncomplicated or complicated UTI will be performed. The Coordinating Center (AMC) prepares drug randomization lists for each study site in advance. All eligible and consenting patients will be randomly allocated to either:

- antibiotic prophylaxis (RCT A and B)

- non-antibiotic prophylaxis: cranberries (RCT-A),

lactobacilli (RCT-B)

- - 1. **Method of blinding**

In each trial two active compounds will be compared. Antibiotics are produced as tablets and non-antibiotics as capsules. Therefore, the “double-dummy”-method is used. Each patient receives 1 tablet and 2 capsules daily, but only one of them (the tablet or the capsules) contains the active substance. Drug packages are labelled with the Study Identification code (SID) by a central pharmacy. Afterwards packages are distributed to the hospital pharmacies of the participating centers. Neither the blinded study team nor the patient will be informed of the treatment until the data collection phase has been completed.

**Checking the success of double-blind conditions**

It is well known that double blinding is easier to strive for than to achieve. Therefore, at 12 months we ask each patient and the study coordinator which drug they think was administered.

**4 Study population**

- 1. **Recruitment and screening method**

Seven Dutch hospitals participate; three university hospitals (Academic Medical Center/Amsterdam, Academic Hospital Maastricht/Maastricht, University Medical Center/Utrecht) and four non-university hospitals (Onze Lieve Vrouwe Gasthuis/Amsterdam, Sint Lucas Andreas Hospital/Amsterdam, Maasland Hospital/Sittard, and Westfries Gasthuis/Hoorn). Urologist, infectious disease specialists or geriatricians from the above-mentioned centers determine patient eligibility and seek informed consent. The specialist will pass contact information from all eligible patients to the study coordinator. The specialist also gives an information letter and two informed consent forms (with one self-addressed envelope) to the patient. Afterwards, the study coordinator contacts the patient and checks if the patient really fulfils the entry criteria. Then the patient will be asked for informed consent. After informed consent the patient has to give or send one signed informed consent form back to the study coordinator, the other stays with the patient.

**4.2 Inclusion criteria and exclusion criteria**

**4.2.1 Inclusion criteria:**

- Women aged 18 years or older
- At least 3 symptomatic urinary tract infections, uncomplicated or complicated (for definitions see Appendix), in the year preceding study inclusion
  - 1. **Exclusion criteria:**

- Life expectancy </= 1 year

- Legally incapable

- A renal transplant in the medical history

- Contraindications for or

relevant interactions with co-trimoxazole (see Table 1)

RCT-A;

- Breastfeeding, pregnancy, or pregnancy wish for the next year

- Contraindications for or relevant interactions with cranberries (see Table 1)

Interactions of patient’s medication with study medication will be evaluated per patient. From each interaction the clinical relevance (risk for a particular patient) will be determined and the study coordinator will deliberate, along with the treating physician, in which way the interaction can be handled best.

Table 1, contra-indications and interactions with co-trimoxazole and cranberries.

| Study medication | Contra-indication | Interaction |
| --- | --- | --- |
| co-trimoxazole | allergy for sulfonamides and/or trimethoprim, severe renal or liver failure ( creatinin *or* ASAT and/or ALAT 5 times the upper limit) serious blood disorders, G6PD-deficiency, acute porphyria | oral anticoagulants, diuretics, sulfonylureumderi-vates, digoxin, methotrexate, fenytoin, procainamid, cyclosporine, folic acid antagonists, para-aminobenzoic acid and derivates |
| cranberries | known renal stones | oral anticoagulants |

If an eligible patient is using or has used cranberries, antibiotics, or estrogens (except oral contraceptives) in the 2 weeks in advance of screening, the patient is offered a “wash-out”-period before randomization.

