**7 Safety**

**7.1 Adverse event**

As described above, all patients will be checked for contra-indications (including renal and liver failure) and relevant interactions for or with the drugs used in this study. Patients with contra-indications for or relevant interactions with study medication will be excluded from the study.

Most reported adverse events from the used antibiotics are: gastro-intestinal disturbances, vaginal symptoms (rash or itching) and allergic skin reactions. Because of the low prescribed dosage of antibiotics, and frequent evaluations, major adverse events are expected to occur very rarely and will be detected early.

The safety of cranberries is considered to be excellent. Some patients may experience a slight laxative effect, depending on the amount ingested (19). Nevertheless, at least one author warned that ingesting a large amount of cranberries over a longer period of time may increase risk of some types of urinary stones in high-risk patients because of the increased urinary excretion of oxalate and slight urinary acidification (20). There are also reported several cases about the possible interaction between cranberries and warfarin (21). For those reasons patients with a history of nephrolithiasis or those who use oral anticoagulants are excluded from RCT-A.

In the few studies using *Lactobacillus rhamnosus GR-1* and *L. reuteri RC-14* no adverse events were reported after oral intake (12).

An adverse event (AE) is defined as any health-related reaction, effect, toxicity or abnormal laboratory result that a participant experiences during the course of a study irrespective of relationship to study treatment. This includes changes in a participant's condition or laboratory results which have or could have a deleterious effect on a participant's health or well-being.

A serious adverse event is defined as any experience that is fatal or life-threatening, permanently disabling, requires in-patient hospitalization, or is otherwise judged to be serious by the study coordinator.

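### Section 7.1 excludes every oral anticoagulant user from RCT-A, but the entry criteria in section 4.2.2 leave the same women to a per-patient judgement and so can admit them

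*Protocol*

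**What the plan says.** Two parts of the protocol deal with oral anticoagulants in RCT-A, the premenopausal trial of cranberry against co-trimoxazole.

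- **Section 7.1 (Adverse event).** It gives the reason, "There are also reported several cases about the possible interaction between cranberries and warfarin", and then the rule: "patients with a history of nephrolithiasis or those who use oral anticoagulants are excluded from RCT-A". The rule has no qualifier.
- **Section 4.2.2 (Exclusion criteria) and Table 1.** There is no separate line for oral anticoagulants. The RCT-A criterion is "Contraindications for or relevant interactions with cranberries (see Table 1". Table 1 has a contra-indication column and an interaction column. In the cranberry row, renal stones are in the first and oral anticoagulants in the second. The co-trimoxazole row also lists oral anticoagulants under interactions.

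The paragraph before Table 1 says how interactions are dealt with: "Interactions of patient’s medication with study medication will be evaluated per patient". It continues: "From each interaction the clinical relevance (risk for a particular patient) will be determined". The next step is that "the study coordinator will deliberate, along with the treating physician, in which way the interaction can be handled best".

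Section 4.1 says who applies the criteria. After the specialist has judged eligibility, "the study coordinator contacts the patient and checks if the patient really fulfils the entry criteria".

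**The concern.** One section makes the exclusion absolute. The section that is used for screening makes it conditional. A woman on an oral anticoagulant whose interaction is thought unimportant, or manageable, meets the entry criteria and yet belongs to a group that 7.1 says is not in the trial.

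This matters for three reasons.

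- Eligibility is checked against the entry criteria, and the unconditional rule is not among them. Seven hospitals recruit, so similar women could be handled differently from one centre to the next.
- Neither arm of RCT-A avoids the problem. Table 1 lists oral anticoagulants against both active drugs, and treatment lasts a year. Under the double-dummy design, "Neither the blinded study team nor the patient will be informed of the treatment until the data collection phase has been completed".
- Section 7.1 offers the exclusion as its answer to the warfarin reports. If these women can enter, that answer is not in force.

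**Working it through.** No figure in the protocol depends on this point, so the check is a comparison of texts, followed by a rough bound on the number of women.

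**1. Is there an exclusion line in 4.2.2 that matches 7.1?** Section 7.1 names two groups.

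| Group named in 7.1 | Place in Table 1, cranberry row | Effect under 4.2.2 |
| --- | --- | --- |
| History of nephrolithiasis | Contra-indication (known renal stones) | Excluded as a contra-indication |
| Use of oral anticoagulants | Interaction | Excluded only if judged relevant for that patient |

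The first group has a counterpart among the contra-indications. The second does not.

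**2. Could every interaction in Table 1 be meant to exclude?** If so, the per-patient paragraph would have no function. It defines relevance as a risk for the individual and ends in a discussion of handling. Nothing in it makes exclusion the required outcome. The two sections agree only if every such judgement ends in exclusion, and 4.2.2 does not say that.

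**3. Does 7.1 simply restate 4.2.2?** Its opening paragraph does: it excludes contra-indications and relevant interactions, the same rule as 4.2.2. The later RCT-A sentence drops the word relevant and is absolute. The conflict lies in that sentence alone.

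**4. How far does it reach?** Only to oral anticoagulants in RCT-A. For the other drugs in Table 1, and for oral anticoagulants in RCT-B, both sections apply the relevant-interaction rule and agree. Oral anticoagulants are 1 of 10 entries in the co-trimoxazole interaction cell and the only entry in the cranberry one.

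**5. How many women?** RCT-A plans 280 women (section 3.2), 140 per arm (section 8.1). The share using oral anticoagulants is not given; the values of p below are assumptions.

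| Assumed share p | RCT-A: 280 × p | Cranberry arm: 140 × p |
| --- | --- | --- |
| 0.5% | 1.4 | 0.7 |
| 1% | 2.8 | 1.4 |
| 2% | 5.6 | 2.8 |

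These are women to whom the conflict would apply, before any per-patient screening. They are not an estimate of women wrongly enrolled.

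**The case against.** The best reply is that the sections can be read together. Section 7.1 opens by referring back to the criteria already described, and cranberry has only one listed interaction. On that view 7.1 is the specific rule that settles the judgement for oral anticoagulants in advance, and the per-patient paragraph is there for the long co-trimoxazole list. Enrolling such a woman would mean overlooking an explicit sentence in the same protocol. She would also have to pass two relevance judgements, one for each active drug.

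That shows what the authors probably intended, but it does not repair the text. Section 4.2.2 has no cross-reference to 7.1, does not limit its per-patient paragraph to co-trimoxazole, and is the list the coordinator screens against.

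The second reply is that other safeguards exist. The general practitioner is told of participation and the patient carries a study card (section 5.4). Monthly questionnaires ask about possible interactions and medication changes (section 6.1). Study drug can be withheld or stopped for a possibly related adverse event (section 7.2). Because the interaction is listed for both active drugs, a clinician knows that it applies whatever the allocation. This stands: the likely harm is smaller than the wording conflict alone suggests. But these measures act after entry, and Table 2 schedules no coagulation test.

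The third reply, that the numbers are assumed and small and that nothing statistical changes, is correct. It limits the weight of the point.

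**Conclusion.** The contradiction is real. Under section 4.2.2 a premenopausal oral anticoagulant user can be eligible; under section 7.1 she is excluded. The per-patient review may in practice turn most of these women away, but nothing in the entry criteria requires it.

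The size is modest: one drug class, one of two trials, and about 1 to 6 women of 280 if the assumed 0.5% to 2% is right. No endpoint, sample size, power or error rate is affected. It should be corrected because it is a safety exclusion that the protocol already promises and its screening text does not enforce. The conclusion rests on the wording alone; the assumed share affects only the count.

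**What to change.** Add use of oral anticoagulants to section 4.2.2 as an explicit exclusion for RCT-A. State that the per-patient evaluation applies to the other interacting drugs in Table 1, and to oral anticoagulants in RCT-B only. Put the matching item on the screening form.

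If the sponsor in fact wants individual judgement for these women, section 7.1 has to be softened instead, and its safety argument can then no longer rest on their absence. The stated rationale points to the first option.

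The cost is one exclusion line, one clarifying sentence and one item on a form.

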**4.3 Withdrawal from study**

Following enrolment, participants may discontinue study participation for the

following reasons:

- Voluntary withdrawal.

- Withdrawal requested by one of the investigators or the treating physician.

Strict distinction is made between withdrawal of study medication (non-adherence) and willingness to participate in data collection efforts. This approach will likely reduce the number of missing data values and facilitate a proper intention-to-treat analysis.

**5 Study Medication**

**5.1 Choice of drugs**

**5.1.1 Antibiotic prophylaxis**

It has been recommended to treat complicated UTIs with antimicrobials which achieve high tissue concentrations, such as trimethoprim-sulfamethoxazole (TMP-SMX or co-trimoxazole). Furthermore, TMP-SMX is also a good prophylactic for patients with a history of uncomplicated recurrent UTIs (8). Therefore, we want to administer TMP-SMX to the study participants.

- - 1. **Non-antibiotic prophylaxis**

In postmenopausal women lactobacilli are often absent. There is a strong positive relation between vaginal-colonization status and the risk of UTI. Therefore, we will use lactobacilli to prevent UTIs in postmenopausal women. We will use *Lactobacillus rhamnosus GR-1* and *L. reuteri RC-14.* Both possess properties that are required to colonize the vagina and inhibit uropathogens.

Premenopausal women will receive cranberry capsules as non-antibiotic prophylaxis. Because of problems with compliance and adherence to therapy with cranberry juice (18), we will use cranberry capsules for this study. Since premenopausal women have normal concentrations of vaginal lactobacilli, it makes no sense to give them additional lactobacilli capsules.

Detailed information about product characteristics and evidence of safety will be described in a separate supplement (Investigational Medicinal Product Documentation).

- 1. **Drug regimen, administration and duration**

RCT-A (premenopausal women). Women in the index group receive one cranberry capsules of 500 mg (in the morning and at bedtime) and one placebo tablet co-trimoxazole of 480 mg (ante noctum). Women in the reference group receive one tablet co-trimoxazole of 480 mg (ante noctum) and one placebo cranberry capsule (in the morning and ante noctum).

RCT-B (postmenopausal women): Women in the index group receive one capsule containing *Lactobacillus rhamnosus GR-1* and *L. reuteri RC-14 (>1*0e9 CFU) (in the morning and ante noctum) and one placebo tablet co-trimoxazole of 480 mg (ante noctum). Women in the reference group receive one tablet co-trimoxazole of 480 mg (ante noctum) and a placebo lactobacillus capsule (in the morning and ante noctum). Thus, in both trials each woman receives once a day one tablet and twice daily one capsule. All capsules and tablets must be taken by mouth for the duration of one year.

- 1. **Drug formulation, supply and distribution**

Cranberry capsules (Cran-Max®) and matching placebos identical in appearance to the cranberry capsules will be obtained from Springfield Nutraceuticals, Oud-Beijerland, the Netherlands. Each active capsule contains 500 milligram of cranberry extract.

The lactobacilli for the lactobacillus capsules (*Lactobacillus rhamnosus GR-1* and *L. reuteri RC-1),* were grown in bulk fermentation vessels under European Approved Good Manufacturing Practice by Chr. Hansen, Denmark. The organisms are freeze- dried and placed in gelatine capsules, with dosage at 10e9 per capsule. Chr. Hansen will also deliver lactobacillus placebos identical in appearance to the capsules with two strains of lactobacilli.

Tablets of co-trimoxazole 480 mg and placebos identical in appearance to the co-trimoxazole tablets are delivered by Tiofarma B.V., Oud-Beijerland, the Netherlands.

Three-monthly, patients receive a package with study medication from the pharmacy in the nearest participating center. Each package is labelled with a SID and contains both the active compound as well as the placebo.

- 1. **Concomitant medications**

Concomitant medication, as listed in table 1, may cause interactions while on study. The general practitioner (GP) will be informed about the participation in the NAPRUTI study. Hence, the GP can take this into account when prescribing drugs. Also patients will receive a card, with relevant study information. They can show it to other healthcare personnel as required.

